### Measures

The instruments include screening, primary outcome, and secondary outcome measures. In addition, potential mediators and predictors of treatment outcome are also assessed. All instruments that had not been available in the languages of the participating sites were translated. The translation versions were checked for consistency with the original version.

#### Screening

##### Mental disorders

Syndrome disorders, according to the DSM-5 criteria, are assessed using the SCID-5-CV [43] or SCID-5-RV [44]. Personality disorders are assessed with the SCID for DSM-5 personality disorders (SCID-5-PD [45]) or SCID for Axis II disorders (SCID-II [46]). The SCID-5-CV is extended with additional disorders and modules from the SCID-5-RV, including gambling disorder, specific phobia, body dysmorphic disorder, intermittent explosive disorder, feeding and eating disorders, somatic symptom and related disorders, and sleep disorders. Additional file 1: Appendix C offers an overview of all syndrome disorders that are assessed with the extended SCID-5-CV. Since the German SCID-5-CV/RV was not yet available during the start of the study, the SCID for DSM-IV Axis I disorders (SCID-I [47]) was assessed temporarily in the German centers. In order to converge to the DSM-5 criteria, missing disorders (e.g., gambling disorder, insomnia disorder) were added to the SCID-I, time periods were changed if needed, and additional items were added to the PTSD module. The SCID-I and SCID-II have demonstrated satisfactory psychometric properties (e.g., [48–50]). Based on an initial psychometric evaluation, the SCID-5-CV and SCID-5-PD have shown adequate psychometric properties [51, 52].

##### Lifetime trauma exposure, index trauma, traumatic memory, and encapsulated belief

The extended self-report version of the Life Events Checklist for DSM-5 (LEC-5 [53]) is used to screen for lifetime exposure to traumatic events. For the purposes of the study, we have added traumas, including exposure to emotional abuse, emotional neglect, and physical neglect (see Additional file 1: Appendix D). Traumatic events that have been endorsed by the participant will be evaluated by the interviewer to ascertain the number of times an event occurred and the age of the participant. In addition to the screening of traumatic events, the index trauma, worst traumatic memory of the index trauma, and encapsulated belief are identified in direct discussion with the participant.

#### Primary outcome

##### PTSD severity

The primary outcome is the change in the severity of the DSM-5 PTSD symptoms between the baseline and follow-up 1 assessments, assessed with the Clinician Administered PTSD Scale for DSM-5 (CAPS-5 [54]). The CAPS-5 is a structured interview consisting of 30 5-point Likert scale items ranging from 0 (absent) to 4 (extreme/incapacitating) rating the 20 DSM-5 PTSD symptoms in the past month. In the current study, the CAPS-5 assesses responses to all traumatic events that have been identified with the LEC-5. The CAPS-5 has demonstrated good reliability and validity [55–57].

The assessment period of the CAPS-5 (i.e., past month) at the T3 assessment overlaps with the treatment period in the once-weekly frequency condition. Therefore, we chose to focus on change between baseline and follow-up 1 instead of baseline and T3 since the follow-up 1 assessment takes place several weeks after treatment has finished and does not overlap with the treatment period (i.e., administered 8–12 weeks after treatment has finished in the once-weekly frequency condition and 16–18 weeks after treatment has finished in the twice-weekly treatment condition).

#### Secondary outcomes

##### Self-reported PTSD symptoms and trauma-related feelings

Self-reported PTSD symptoms are measured using the PTSD Checklist for DSM-5 (PCL-5 [58]). The PCL-5 consists of 20 5-point Likert scale items ranging from 0 (not at all) to 4 (extremely). We created two versions of the PCL-5; one version assessing self-reported PTSD symptoms with respect to the index trauma and the other one for all traumatic experiences except of the index trauma. The time frame was changed from the past month to the past week. Psychometric properties of the PCL-5 were found to be good [59–61].

Seven single-item scales were added to the PCL-5 [38, 62], see Additional file 1: Appendix D. Six items were included to assess trauma-related feelings (i.e., feelings of shame, anger, guilt, disgust, sadness, and anxiety) with respect to the index trauma and for all traumatic experiences except of the index trauma. An additional item was included to assess feelings of happiness in the past 7 days, for secondary analysis purposes. The additional items will not be used for computation of the total PCL-5 score.

##### PTSD-related cognitions

The Posttraumatic Cognitions Inventory (PTCI [63]) is a 33-item questionnaire measuring trauma-related cognitions across three domains (i.e., negative cognitions about self, negative cognitions about the world, and self-blame). The items are rated on a 7-point Likert scale ranging from 1 (totally disagree) to 7 (totally agree). The PTCI has demonstrated satisfactory psychometric properties [63].

##### Depressive symptoms

Depressive symptoms during the last 2 weeks are measured by the Beck Depression Inventory II (BDI-II [64]). The BDI-II consists of 21 items containing a list of four statements with regard to a particular symptom of depression. The BDI-II has shown good psychometric properties [65].

##### Guilt and shame

An eight-item questionnaire was developed based on the Personal Feelings Questionnaire 2 (PFQ2 [66]) and the Adapted Shame and Guilt scale (ASGS [67]) to assess feelings of guilt and shame in the past 4 weeks (see Additional file 1: Appendix E [68]). The items are rated on a 5-point Likert scale ranging from 0 (never) to 4 (daily). A validation study is currently running.

##### Anger

Anger is measured using the Self-Expression and Control Scale (SECS [69]) and the Hostility subscale of the Symptom Checklist-90-Revised (SCL-90-R [70, 71]). The SECS measures anger expression and anger control and consists of 40 items scored on a 4-point Likert scale ranging from 1 (almost never) to 4 (almost always). Previous research has demonstrated good psychometric properties [69, 72]. The Hostility subscale of the SCL-90-R contains six 5-point Likert scale items ranging from 0 (not at all) to 4 (extremely) and assesses anger related thoughts, feelings, and actions. The subscale demonstrated satisfactory validity and reliability [73, 74].

##### Happiness

Happiness is assessed by a single 7-point Likert scale item ranging from 1 (completely unhappy) to 7 (completely happy) which measures general happiness in the weeks prior to the assessment [75]. Reliability and validity ranged from good to excellent [75].

##### Depressive attributions

The Depressive Attributions Questionnaire (DAQ [76]) measures depressogenic attributions. The DAQ consists of 16 items measuring helplessness and negative internal, stable, and global attributions. The items can be rated on a 5-point Likert scale ranging from 0 (not at all) to 4 (very strongly). Earlier research has demonstrated good psychometric properties [76, 77].

##### Dissociative experiences

Dissociative experiences are assessed with the Dissociative Experiences Scale Taxon (DES-T [78]), a brief version of the DES [79]. The DES-T contains eight items rated on an 11-point Likert scale ranging from 0% (never) to 100% (always) at 10% intervals. Psychometric properties of the DES-T are satisfactory [80].

##### Quality of life

Quality of life is measured using the 5-level EuroQol 5D version (EQ-5D-5L [81]) and the Mental Health Quality of Life seven-dimensional Questionnaire (MHQoL-7D [82]). The EQ-5D-5L assesses five health state dimensions (mobility, self-care, usual activities, pain/discomfort, and anxiety/depression), whereby each dimension is divided into five severity levels ranging from no problem to extreme problems. The EQ-5D-5L has shown to be a valid and reliable measure [83].

The MHQoL-7D was recently developed and assesses quality of life in people with mental health problems. The MHQoL-7D contains seven quality of life domains (self-image, independence, mood, relationships, daily activities, physical health, and hope) divided into four severity levels and a visual analog scale (VAS) assessing patient’s psychological well-being. Currently, a study into the psychometric properties of the MHQoL-7D among PTSD patients is running. The MHQoL-7D will only be included in the analysis if it is demonstrated to be a psychometrically sound instrument. As the recruitment of patients started before the MHQoL-7D was available, the quality of life instruments are assessed in a subset of the patients.

##### Complex PTSD symptoms

The 18-item International Trauma Questionnaire (ITQ [84]) measures complex PTSD (CPTSD) symptoms according to the diagnostic formulation published in the 11th revision of the International Classification of Diseases (ICD-11 [85]). To minimize participant burden, only nine items measuring the three Disturbances in Self-Organization (DSO) clusters (i.e., affective dysregulation, negative self-concept, and interpersonal problems) and functional impairments related to DSO symptoms are administered. The combined data of PCL-5 scores and DSO scores will provide dimensional scoring, as well as diagnostic information (i.e., diagnosis of PTSD or CPTSD based on the ICD-11 diagnostic rules). The ITQ has demonstrated adequate internal reliability and validity [84, 86]. Recruitment of patients had commenced before the ITQ was included and, therefore, the ITQ is assessed in a subset of the patients.

##### General, social, and societal functioning

General, social, and societal functioning is assessed by the 12-item World Health Organization Disability Assessment Schedule 2.0 (WHODAS 2.0) interview version [87]. The WHODAS 2.0 assesses experienced difficulties in six major life domains (i.e., cognition, mobility, self-care, getting along, life activities, and participation) in the past 30 days on a 5-point Likert scale ranging from 1 (none) to 5 (extreme or cannot do). The WHODAS 2.0 has shown good psychometric properties [87].

##### Demographics

General patient characteristics (e.g., age, ethnicity, marital status, educational level) will be collected using a semi-structured demographic interview. Additional information will be collected with regard to patient's employment situation, medication use, substance use, and use of psychological treatments other than the study treatment (i.e., ImRs or EMDR).

#### Mediators

Potential mechanisms underlying the presumed effect of session frequency on treatment outcome include memory, learning, therapeutic alliance, motivation, reluctance, and avoidance.

##### Memory

Memory of the previous session is assessed by a recently developed memory test (see Additional file 1: Appendix F) in which patients and therapists are asked to think back to what happened in the previous session and to describe as precisely as possible the most important issues of the previous session.

##### Mediator items

The mediator items have been specifically developed for the study (see Additional file 1: Appendix G) and include nine 100 mm VAS items assessing memory and learning (two items: memory of the previous session and time to process), therapeutic alliance (three items: working alliance, connection, and support), motivation (one item), and reluctance and avoidance (three items: reluctance to participate, difficulty of the treatment, and optimism about the final outcome of the treatment). In addition to these nine items, one additional item is filled out by the patient about life events that may interfere with the treatment.

##### Traumatic memory and encapsulated belief ratings

Traumatic memory vividness, distress and valence, and credibility of the encapsulated belief are potential mechanisms of change of EMDR and ImRs [38] and assessed by a semi-structured imagery interview [88–91]. Participants are asked to recall the worst traumatic memory of the index trauma, identified during the screening procedure. After the image of the memory has been elicited, the vividness and controllability of the memory and the degree of distress related to the memory are rated on a 100 mm VAS. In addition, the valence of the traumatic memory (e.g., anger, sadness, shame) is evaluated on eight 5-point Likert scale items ranging from 0 (not at all) to 4 (extremely). Finally, participants rate to what extent they believe their encapsulated belief is true. This procedure has been used in previous research [38].

#### Predictors

Candidate predictors of (differential) treatment response were selected based on the literature, expert consensus, and preliminary analyses of the IREM study [11]. The predictors are assessed during the baseline assessment. Only the measures that are not part of the screening and secondary outcome measures are briefly described below.

##### Childhood maltreatment

The Childhood Trauma Questionnaire-Short Form (CTQ-SF [92]) assesses the severity of five types of childhood maltreatment (i.e., emotional abuse, physical abuse, sexual abuse, emotional neglect, and physical neglect). The CTQ-SF consists of 28 items rated on a 5-point Likert scale ranging from 1 (never true) to 5 (very often true). Several studies have demonstrated satisfactory psychometric properties (e.g., [92–94]).

##### Experiential avoidance

The Brief Experiential Avoidance Questionnaire (BEAQ [95]) assesses experiential avoidance across six different domains (i.e., behavioral avoidance, distress aversion, suppression, procrastination, repression/denial, and distress endurance). The BEAQ consists of 15 6-point Likert scale items ranging from 1 (strongly disagree) to 6 (strongly agree) and has demonstrated satisfactory psychometric properties [95].

##### Readiness to change

Readiness to change is measured by the subscales Contemplation and Action of the 24-item version of the University of Rhode Island Change Assessment (URICA [96–98]). Each subscale consists of six items that are scored on a 5-point Likert scale ranging from 1 (strongly disagree) to 5 (strongly agree). Both subscales have demonstrated satisfactory internal consistency [99].

##### Social problems

Social problems (e.g., housing problems, unemployment, social isolation) are assessed in direct discussion with the participant by using the social problems list, derived from the Improving Access to Psychological Therapies (IAPT) program [100].

##### Openness to experience

The openness to experience subscale of the Big Five Inventory (BFI [101]) is a 10-item scale that measures openness to experience. Each item can be rated on a 5-point Likert scale ranging from 1 (disagree strongly) to 5 (agree strongly). The subscale has demonstrated satisfactory validity and reliability [102].

##### Working memory

An adapted version of the subtask Doing sums of the Groningen Intelligence Test (GIT [103]) is used as a proxy for working memory. This task involves the correct completion of as many adding sums as possible in 1 min. The test-retest reliability of the subtask Doing sums was satisfactory in previous research [104].

##### Willingness to talk about traumatic experiences

Willingness to talk about traumatic experiences is assessed by two 100 mm VAS items specifically developed for the study (see Additional file 1: Appendix H).

##### Schema mode ratings: detached protector and suspicious overcontroller

Two schema modes (i.e., detached protector mode and suspicious overcontroller mode) are measured using two subscales of the Schema Mode Inventory 1 and 2 (SMI [105, 106]). Both subscales consist of nine 6-point Likert scale items ranging from 1 (never or almost never) to 6 (all of the time) and demonstrated acceptable psychometric properties [107].

##### Mental imagery capacity

The Gordon Test of Visual Imagery Control (TVIC [108]) is used to assess mental imagery capacity. This TVIC consists of 12 3-point Likert scale items (yes, no, and unsure) measuring the ability to visualize and manipulate mental images. In addition to the Likert scale, we also measure the time it takes the participant to visualize the scenes. Finally, we have added two 100 mm VAS items measuring how well the participant sees the mental scenes that were described and how difficult it was for the participant to visualize the different scenes (see Additional file 1: Appendix D). The TVIC has shown acceptable to satisfactory validity and internal consistency [109–111].

##### Avoidance of shame and guilt

The extent to which people tend to avoid sharing issues they feel ashamed about and issues they feel guilty about is assessed by two 100 mm VAS items specifically developed for the study (see Additional file 1: Appendix I).

##### Attachment style

Participant’s general attachment style is measured by the Relationship Structures Questionnaire (ECR-RS [112]), a brief version of the Experience in Close Relationships-Revised (ECR-R [113]). The ECR-RS consists of nine 7-point Likert scale items ranging from 1 (strongly disagree) to 7 (strongly agree) and assesses attachment-related avoidance and attachment-related anxiety. The ECR-RS has demonstrated good psychometric properties, comparable to the ECR-R [112].

##### Frustration tolerance

Frustration tolerance is assessed by the Frustration tolerance scale of the Personality Data Form (PDF [114]). This subscale consists of 13 3-point Likert scale items ranging from 1 (often) to 3 (seldom). Shorkey and Sutton-Simon [115] have found initial evidence for the reliability and validity of the PDF.

##### Rumination

Rumination is measured by the Perseverative Thinking Questionnaire (PTQ [116]). The PTQ consists of 15 5-point Likert scale items ranging from 0 (never) to 4 (almost always) and assessing the frequency of dysfunctional, repetitive thinking. The PTQ has demonstrated good psychometric properties [116, 117].

### Statistical analyses

The statistical analyses will be performed according to the intention-to-treat principle. Change in the primary and secondary outcome measures and the relative effectiveness of the two frequency conditions (twice-weekly frequency condition versus once-weekly frequency condition) will be analyzed using mixed regression analyses. By using mixed regression analysis, all available data will be used, and dependencies among observations nested within individuals will be taken into account. Appropriate forms of the mixed regression models will be selected, based on the variable type (e.g., scale, count, dichotomous) and taking into account the distribution of the residuals. To assess the comparative effectiveness of EMDR and ImRs and whether treatment type moderates the effect of session frequency, additional terms will be added to the model. In addition to the primary analyses based on the intention-to-treat principle, a completers analysis focused on the change in the primary outcome measure will be conducted by excluding patients who discontinued treatment or deviated from the protocol (e.g., duration of more than 16 weeks in the once-weekly frequency condition, other psychological treatment next to the study treatment, unstable level of medication during the treatment period). No interim analyses are planned. Finally, to examine underlying change mechanisms of session frequency (i.e., memory and learning, therapeutic alliance, motivation, and reluctance and avoidance), advanced mediation analysis will be performed (e.g., mixed regression for Granger Causality models [118]).

The additional substudies will be analyzed using different statistical methods. To study (differential) mechanisms of change of EMDR and ImRs (i.e., the strength of the encapsulated belief, and the vividness and valence of the traumatic memory of the index trauma), mediation analysis will be conducted using Granger Causality models. In addition, mixed regression analysis will be used to investigate whether comorbid personality disorder psychopathology and trauma characteristics are related to treatment effects. The role of emotions, cognitions, memory, and learned helplessness in altering PTSD symptoms over time will be examined using advanced mediation analyses (e.g., mixed regression for Granger Causality models [118]). Furthermore, a two-step approach will be used to determine the optimal treatment type (EMDR versus ImRs) and frequency (twice-weekly versus once-weekly) for a particular patient. First, we will examine which of the candidate predictors predict what treatment and which frequency will be more beneficial. Different variable selection approaches can be applied, including bootstrapping procedures [119], a Random Forest machine learning approach [120], and the domain approach outlined by Fournier et al. [121]. Second, a prediction model will be built based on the identified predictors to generate individual treatment recommendations geared to predict the primary outcome measure (i.e., PTSD severity). Since statistical methods for the selection of variables and generating individual treatment recommendations are still in development, we will select the optimal methods at the time of the analyses. Finally, to investigate the network structure of (complex) PTSD symptoms at baseline and changes in the network structure of patients as a consequence of treatment, network analysis and longitudinal comparisons between networks will be conducted (e.g., [122, 123]).

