#### Secondary objectives

The IREM-Freq study has several secondary objectives. These include investigating (1) the comparative effectiveness of EMDR and ImRs, (2) whether treatment type (i.e., EMDR versus ImRs) moderates the effect of session frequency, (3) the hypothesized change mechanisms underlying the effects of session frequency on treatment outcome (i.e., memory and learning, therapeutic alliance, motivation, and reluctance and avoidance), (4) the (differential) change mechanisms of EMDR and ImRs, (5) potential predictors of treatment outcome and PTSD severity, (6) the role of emotions, cognitions, and memory in the change in PTSD symptoms, (7) the impact of trauma-focused treatments on learned helplessness, (8) the optimization of treatment selection through identifying patient characteristics that predict treatment response across treatment types (EMDR and ImRs) and treatment frequencies (twice-weekly and once-weekly sessions), (9) the perspectives of patients and therapists on the treatments, (10) the network structure of PTSD symptoms, and (11) sudden treatment gains.

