After the screening assessments are completed, a final check of the inclusion and exclusion criteria is performed by the junior investigator and the patient is randomized by an independent staff member of the sponsor. After randomization, the site investigator of the center is informed of the patient’s allocated treatment condition and searches for a suitable therapist, taking into account the availability of the patient and the preference of the patient for a male or female therapist. At the same time, the baseline assessment (T1) is administered by a research assistant blinded to the patient’s allocated condition. If the time between the start of the treatment and the baseline assessment is more than 5 weeks, an additional assessment (i.e., waitlist assessment) is conducted before the patient starts with the treatment. After the baseline assessment (and, if applicable, the waitlist assessment) is completed and a therapist has been found, the patient starts the treatment. The session frequency of the treatment (i.e., twice a week or once a week) will be revealed to the patient with the invitation for the first session, but the treatment type (i.e., EMDR or ImRs) is not communicated to the patient until the first treatment session.

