### Allocation

An independent staff member of the sponsor, not involved in the study, randomizes the patients per center to one of the four conditions (i.e., EMDR once a week, EMDR twice a week, ImRs once a week, or ImRs twice a week) using a computer-generated list. This list was created before the first patient was randomized based on block randomization (*N* = four or eight, with block size randomized) per center, and stratified by gender, to guarantee the balance between conditions per site and over time, and to control for the gender distribution. By randomly varying the block size, the unpredictability of the allocation sequence is enhanced. Only the independent staff member has access to the random list and will keep the list until the end of the research to ensure allocation concealment. The condition will be revealed to the patient with the invitation for the first treatment session (session frequency) and during the first treatment session (treatment type).

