#### Therapists, training, and supervision

All therapists in this study are psychologists, psychotherapists, or psychiatrists trained in ImRs, EMDR, or both treatment types. In order to participate, EMDR therapists must have completed a level 1 basic training in EMDR and ImRs therapists were required to complete a basic training course in cognitive behavioral therapy (CBT). In addition, all therapists must have completed an additional 2-day training in EMDR or ImRs for PTSD related to childhood trauma focusing on the treatment protocols as investigated in the study.

Before therapists can start with the treatment, they are required to demonstrate their competence to deliver the treatment with pilot patients. These pilot treatments are evaluated during peer supervision and by the site investigator of the center. During the study, therapists are obliged to attend weekly peer supervision or supervision by an EMDR or ImRs supervisor at their site. Moreover, therapists and site supervisors can consult an expert for questions regarding EMDR ([name]) and ImRs ([name]). Treatment recordings can be used for supervision. In addition, treatment recordings are also assessed for treatment integrity using adherence scales (EMDR: modified EMDR Therapy Fidelity Rating Scale [41], and ImRs: ImRs Therapist Adherence and Competence Scale [42]).

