Second, the study is not powered to reliably detect (≥ 80% power) small effects of session frequency, or the interaction between frequency and treatment method. Finally, the training requirements for therapists differ between the treatments types and there is no budget available for intensive supervision by experts outside the treatment centers. However, experts in the field of EMDR ([name]) and ImRs ([name]) are available for consultation. Moreover, these conditions reflect clinical practice and, consequently, enhance generalizability of the findings to “real-world” settings.

In conclusion, this study is the first to compare treatment outcomes of twice-weekly versus once-weekly sessions of EMDR and ImRs for adult patients with PTSD related to childhood trauma. Research into the effect of session frequency on treatment outcome in Ch-PTSD patients is highly needed since there are indications that session frequency is related to the effectiveness of trauma-focused treatments for PTSD. Moreover, by investigating underlying mechanisms and predictors of (differential) treatment outcome, we will gain more insight into for whom a treatment works and how. This study will, therefore, significantly extend our knowledge on trauma-focused treatments for Ch-PTSD and, more specifically, the role of session frequency.

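### The stated mixed model handles only within-patient dependence, so the EMDR versus ImRs test may be anti-conservative to the extent that therapists deliver one treatment only

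*Protocol article*

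**What the plan says.** The Statistical analyses section of the protocol article gives mixed regression as the method for the primary and secondary outcomes. It names one source of correlation: "dependencies among observations nested within individuals will be taken into account". The treatment-type questions go into the same model: "To assess the comparative effectiveness of EMDR and ImRs and whether treatment type moderates the effect of session frequency, additional terms will be added". Under Secondary objectives, this comparison comes first in the list: "These include investigating (1) the comparative effectiveness of EMDR and ImRs".

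Three other sections bear on who treats whom.

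- Therapists, training, and supervision: "All therapists in this study are psychologists, psychotherapists, or psychiatrists trained in ImRs, EMDR, or both treatment types". Entry training is set separately for EMDR and for ImRs therapists.
- Allocation: an independent staff member "randomizes the patients per center to one of the four conditions". The patient is the unit of randomisation.
- Procedure: once told the allocation, the site investigator "searches for a suitable therapist, taking into account the availability of the patient". The therapist is therefore chosen after randomisation and not at random.

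The article mentions no therapist term in the model, and it does not say that therapist effects will be left out. It does not report how many therapists take part, how many patients each treats, or how many deliver both treatments.

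**The concern.** A therapist who delivers only EMDR or only ImRs is nested in that arm. Patients of one therapist tend to have more similar outcomes than patients of different therapists. Where the therapist is nested in the arm, this similarity adds to the variance of the difference between arms. A model that clusters only on the patient counts those patients as independent and reports too small a standard error for EMDR versus ImRs. The risk is a claim that one treatment is better, made with an error rate above the nominal 5%.

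A therapist who delivers both treatments contributes a within-therapist comparison, and the therapist's own effect then cancels. The direction and size of the problem therefore depend on the mix of single-treatment and dual-treatment therapists, which the article does not give.

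The frequency contrast is in a different position. Nothing in the article ties a therapist to once-weekly or twice-weekly sessions, so that comparison can be made largely within therapists.

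**Working it through.** **The plan's own figures.** The Sample size section uses an unclustered two-sided t-test at 0.05 for frequency comparisons. With the exact noncentral t:

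- d = 0.50, 100 per group: power 0.940 (stated 94%)
- d = 0.40, 100 per group: power 0.804 (stated 80%)
- d = 0.57, 50 per group: power 0.806 (stated 80%)

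All three reproduce. None is stated for EMDR versus ImRs.

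**Inputs for the treatment-type contrast.** From the article: two-sided alpha of 0.05, and equal allocation, so about 100 versus 100 at N = 200. Assumed, because the article gives no values:

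- m, patients per therapist: 6 as the central value, range 3 to 10
- ICC, the therapist share of outcome variance: 0.05 as the central value, range 0.01 to 0.10
- f, the share of patients seen by single-treatment therapists: 1, 0.5 and 0
- caseloads are equal, dual-treatment therapists split their patients evenly, and therapists do not differ in how much better they do with one treatment than the other

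**Formulas.**

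- Design effect: DE = f × [1 + (m − 1) × ICC] + (1 − f) × (1 − ICC)
- True standard error / unadjusted standard error = √DE
- True type I error = 2 × [1 − Φ(1.96/√DE)]

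**Central case, m = 6, ICC = 0.05.**

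| Structure | DE | √DE | 1.96/√DE | True type I error |
|---|---|---|---|---|
| Fully nested (f = 1) | 1 + 5 × 0.05 = 1.25 | 1.118 | 1.753 | 8.0% |
| Half nested (f = 0.5) | 0.5 × 1.25 + 0.5 × 0.95 = 1.10 | 1.049 | 1.869 | 6.2% |
| Fully crossed (f = 0) | 1 − 0.05 = 0.95 | 0.975 | 2.011 | 4.4% |

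**Range over m = 3 to 10 and ICC = 0.01 to 0.10.**

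| Structure | DE | True type I error |
|---|---|---|
| Fully nested | 1.02 to 1.90 | 5.2% to 15.5% |
| Half nested | 1.005 to 1.40 | 5.1% to 9.8% |
| Fully crossed | 0.99 to 0.90 | 4.9% to 3.9% |

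**Where the sign changes.** Setting DE = 1 gives f × m × ICC = ICC, so f = 1/m whatever the ICC. With 6 patients per therapist, the unadjusted test is anti-conservative once more than 1/6 (about 17%) of patients are with single-treatment therapists. The break-even share is 1/3 at m = 3 and 1/10 at m = 10.

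The calculation uses the normal distribution and so leaves out the further effect of having few therapists. Small-sample degrees of freedom deal with that.

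**The case against.** The strongest reply is that the article is silent rather than wrong. The quoted clause explains why mixed regression was chosen and need not be a full list of random effects. The section also leaves the form of the models open, and random-effects detail often sits in an analysis plan, which is not shown here. This stands in part: a reader might infer that the plan ignores therapists, and the text does not say so. But it does state which dependence is handled, and it puts the treatment-type test in that same model. Followed as written, the test has no protection against therapist clustering.

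A second reply is that a reader might infer that most of the EMDR versus ImRs contrast lies between therapists. The documents do not support that. Training in both treatments is allowed and no shares are given. With full crossing, the unadjusted standard error is slightly too large.

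A third reply is that several features should hold therapist variance down: treatment manuals, shared protocol training, pilot patients, weekly supervision and adherence ratings. Randomisation within centres also removes most of the between-centre part of therapist differences from the contrast. These points favour the lower end of the ICC range, but they do not make the ICC zero.

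Finally, the Discussion concedes that "the training requirements for therapists differ between the treatments types". This is a systematic difference between the arms. It is not evidence of variance among therapists within an arm, and a random effect would not remove it, so it adds little to the case.

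**Conclusion.** The point holds in a limited form. The stated model covers only within-patient dependence, and some or much of the EMDR versus ImRs contrast may lie between therapists. At 6 patients per therapist and an ICC of 0.05, the true type I error is about 8.0% if fully nested, 6.2% if half nested and 4.4% if fully crossed. These figures rest on assumed caseload, ICC and nesting, because the article gives none of them.

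Only secondary objective 1 is affected. Two further inferences are not supported:

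- **That the stated 80% power should be lower.** By the normal approximation, a fully nested contrast with DE = 1.25 would have power of about 72% at d = 0.40: Φ(0.40/(√0.02 × 1.118) − 1.96) = Φ(0.570) = 0.716. But the article's 80% is stated for the frequency comparison, so this corrects no stated figure.
- **That the primary frequency result is compromised.** No section links therapists to a session frequency, and nothing shows that this contrast is harmed.

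**What to change.** - Add a therapist random intercept to the mixed models, with a therapist-by-time term if it can be estimated. Baseline is measured before treatment starts, so a therapist's influence acts on change. If baseline is one of the modelled outcomes, the therapist-by-time term carries that influence. If baseline is a covariate, the intercept does.
- Use Satterthwaite or Kenward-Roger degrees of freedom for the treatment-type contrast.
- Report the therapist ICC, the number of therapists, their caseloads, and how many deliver one or both treatments.
- If the analysis plan already has such a term, one confirming sentence is enough.

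The cost is low. Therapists complete questionnaires and session records for their patients, so the link from patient to therapist should already exist and no new assessment is needed. The downside is slightly wider intervals for EMDR versus ImRs. If the ICC is close to zero, little is lost.
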